### Ethics and safety

The trial has been approved by the Ethics Committee of the West China Hospital, Sichuan University (2021 No. 376), and registered on ClinicalTrials.gov (registration number NCT04922853). Each participant has signed an informed consent form (ICF, Additional file 6) before enrollment. We will request consent for the review of participants’ medical records and for the collection of blood samples to detect potential hematopoietic inhibition or impairment of liver or kidney function, and tumor markers, at least including CEA and CA19-9, which will be recorded every cycle. Resected rectal specimens will also be stored for pathological review. Participants have the right to quit the study at any time without any reason.

### Monitoring and reporting

Information of the coordinating center has been listed in Additional file 1. Each sub-center will be responsible for identifying potential patients and taking their consent independently, while center randomization will be made subsequently after inclusion by West China Hospital of Sichuan University. Also, each sub-center is responsible for monitoring the safety of their included patients, and the West China Hospital of Sichuan University is responsible for the overall COPEC trial. The trial steering committee (TSC) is composed of professional investigators of each sub-center and is responsible for supervising the trial. The regular meeting of TSC is set every 6 months to oversee conduct and progress.

Patients are covered by health insurance in case the adverse effects from NCT occur and will be withdrawn from the trial if they are evidenced sufferings risks beyond expected based on medical reasons. Detected serious adverse events will be submitted to the related medical ethical committee for further evaluation within 1 month after the occurrence. All adverse events will be updated on ClinicalTrials.gov. Investigators can examine the detail of the adverse events online.

Adverse events mainly include tumor progression and serious chemotherapy adverse effects during CAPOX. Tumor progression is defined as a tumor longitudinal size increase greater than 20%. Patients will be advised to withdraw from the trial if the tumor is determined a progressive disease (PD). The chemotherapy-related adverse effect is graded according to CTCAE 5.0, and adverse effects graded 3–4 are defined as serious adverse effects. The occurrence and recording of adverse reactions are responsible for the sub-center and follow the principles below:If a 1/2° adverse reaction occurs, no special treatment is required.Capecitabine/oxaliplatin should be discontinued and corresponding symptomatic treatment should be given when 4° leukopenia, 3° adverse reactions of the digestive tract, 2° anemia and thrombocytopenia, and 2° liver and kidney function impairment occur. If the adverse reactions decreased to 0 ~ 1° within 5 days after treatment, the original dose of capecitabine/oxaliplatin can be restored. Otherwise, capecitabine/oxaliplatin should be reduced to 75%. Capecitabine/oxaliplatin treatment should be discontinued if these adverse reactions persist for more than 3 days after symptomatic treatment and dosage reduction or other adverse reactions above 2° occur.When other 3° adverse reactions occur, the treatment principle is the same as the corresponding 2° adverse reactions.Chemotherapy should be stopped in case of any 4° adverse reactions other than leukopenia occurring.

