8)	The main organ function is normal and meets the following standards: (1) blood routine criteria: HB ≥ 9 g/dL, WBC ≥ 3.5/4.0 × 10^9^/L, neutrophil ≥ 1.5 × 10^9^/L, PLT ≥ 100 × 10^9^/L; (2) blood biochemical criteria: Crea and BIL ≤ 1.0 times the upper limit of normal value (ULN), ALT and AST ≤ 2.5 times the upper limit of normal value (ULN), alkaline phosphatase (ALP) ≤ 2.5 × UNL, total bilirubin (Tbil) ≤ 1.5 × UNL
9)	No history of 5-Fu and platinum drug allergy
10)	Females of childbearing age must undergo a pregnancy test (serum or urine) 7 days before enrollment with a negative result and are willing to use appropriate contraceptive methods during the trial and 8 weeks after the last administration
11)	Patients voluntarily join the study and sign informed consent forms with good compliance and follow-up
Exclusion criteria joined	
1)	Patients considering lynch syndrome
2)	Patients who do not consider metastasis in the initial diagnosis but proved to be distant metastases during the treatment
3)	Previously or concurrently suffering from other malignant tumors (including concurrent colon cancer), except for cured skin basal cell carcinoma and cervical carcinoma in situ
4)	Pregnant or nursing women
5)	Lateral lymph nodes ≥ 7 mm
6)	Patients with severe cardiovascular disease and diabetes difficult to control
7)	Patients with mental disorders
8)	Patients with severe infection
9)	Patients undergoing thrombolysis/anticoagulation therapy with bleeding diathesis or coagulation dysfunction, or suffering aneurysm, stroke, transient ischemic attack in the past year
10)	Patients with a history of kidney disease, urinary protein, or clinically abnormal renal function
11)	Patients with a history of gastrointestinal fistula, perforation, bleeding, or severe ulcer
12)	Patients with severe gastrointestinal diseases that affect the absorption of oral chemotherapy drugs
13)	Patients participating in another clinical trial within 4 weeks before treatment
14)	Patients pathologically diagnosed with mucinous component or the signet-ring cell carcinoma
Withdrawal criteria	
1)	Patients refusing further treatment
2)	Patients having severe adverse reactions to chemotherapy and being unable to complete 2 cycles of chemotherapy

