### Data collection

Clinical, imaging, and follow-up data will be collected prospectively in the case report forms (Additional file 4) and reserved in the O-trial online database (https://plus.o-trial.com/), which is daily maintained by [name] and [name]. The O-trial online database is a secure, password-protected database and can be only accessible to authorized project staff.

Details of the evaluation items and time points have been shown in Table 2. During CAPOX, blood routine and biochemistry will be examined weekly to detect potential hematopoietic inhibition or liver or kidney function impairment. Tumor markers, at least including CEA and CA19-9, will be recorded every cycle. Imagological examination, including chest CT, abdominal enhanced CT, rectal MRI, and TRUS will be re-evaluated every 2 cycles.

**Table 2 Tab2:** Details of the evaluation items and time points

	Screening	After 2 cycles of CAPOX (4 cycles)	Preoperative evaluation	Intraoperative evaluation	Postoperative evaluation	Follow-up visit
Colonoscopy	×					
Chest CT	×	×	×			×
Abdominopelvic enhanced CT	×	×	×			×
Pelvic MRI	×	×	×			
TRUS	×	×	×			
Blood routine	×	×	×			×
Blood biochemical indicators	×	×	×			×
Tumor markers^a^	×	×	×			×
Intraoperative complications				×		
Blood loss				×		
Operation time				×		
Surgical approach				×		
Perioperative complications					×	
Patient recovery					×	
Hospitalization time					×	
pTRG					×	

*TRUS* Transrectal ultrasonography, *pTRG* Pathological tumor regression grade

^a^At least includes CEA and CA19-9

Surgical information including tumor location and involvement, intraoperative stages, lymph node metastasis, operation times, intraoperative time, and complications will be recorded in detail in the surgical records. Perioperative complications are stratified by the Clavien-Dindo system. Resected rectal specimens will be fixed on a foam plate and sent to pathologists to determine the circumferential resection margin (CRM) and pTRG).

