### Endpoints

The primary endpoint is the proportion of patients with pTRG3, which is determined postoperatively by each sub-center and verified by the primary center.

The secondary endpoints include (1) the proportion of patients with TRG on MRI (mrTRG) (1–5) after 2 cycles/4 cycles of CAPOX; (2) the proportion of patients with pTRG (0–2); (3) survival prognosis of patients with different pTRG, containing disease-free survival (DFS), local recurrence rate (LR), distant recurrence rate (DR), and overall survival (OS); (4) 3-year DFS and OS of patients with different pTRG; (5) the predicted imaging indicators of pTRG; (6) the accuracy of pTRG judged by imaging; (7) the adverse effects of chemotherapy; (8) the incidence of perioperative complications; and (9) the QOL of patients during chemotherapy and after surgery.

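### Progression during CAPOX is defined by tumour lengthening alone, and metastasis found on treatment is handled separately as an exclusion, so a progression count under the stated definition omits distant progression

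*Protocol article*

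**What the plan says.** The relevant statements are spread over several sections of the protocol article.

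- **Monitoring and reporting, on what an adverse event is:** "Adverse events mainly include tumor progression and serious chemotherapy adverse effects during CAPOX".
- **Same section, on progression:** "Tumor progression is defined as a tumor longitudinal size increase greater than 20" per cent. No new-lesion, nodal or distant component is given, and no published response criteria are cited.
- **Same section, on the consequence:** "Patients will be advised to withdraw from the trial if the tumor is determined a progressive disease (PD"). PD has no definition of its own.
- **Same section, on publication:** "All adverse events will be updated on ClinicalTrials.gov".
- **Table 1, exclusion criterion 2:** "Patients who do not consider metastasis in the initial diagnosis but proved to be distant metastases during the treatment". The withdrawal criteria in the same table cover refusal of further treatment and inability to complete 2 cycles because of toxicity. They do not mention metastasis.
- **Data collection:** "Imagological examination, including chest CT, abdominal enhanced CT, rectal MRI, and TRUS will be re-evaluated every 2 cycles".
- **Endpoints:** secondary endpoint 3 is "survival prognosis of patients with different pTRG, containing disease-free survival (DFS), local recurrence rate (LR), distant recurrence rate (DR), and overall survival (OS"). The pathological grade is available only after surgery: "The primary endpoint is the proportion of patients with pTRG3, which is determined postoperatively by each sub-center and verified by the primary center".

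**The concern.** New distant metastasis during neoadjuvant chemotherapy is the most serious way in which a tumour can progress, and the trial schedules the CT scans that would show it. Yet the stated definition of progression looks only at tumour length, and the stated rule for metastasis is an exclusion. Nothing in the article links the two.

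What is at stake is the reading of a safety count. The Discussion argues that prolonged chemotherapy in insensitive patients may delay treatment they need, with oncological consequences. Someone comparing 2 with 4 cycles would want metastasis on treatment to appear as progression in the arm to which the patient was randomised. Under the rules as written, it need not.

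**Working it through.** The article states no figure for progression or for metastasis on CAPOX, so there is nothing to reproduce. The check is to follow one patient through the stated rules.

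**Step 1. When exclusion criterion 2 acts.** Under Randomization and intervention, central randomisation takes place as soon as enrolment is settled, which is before CAPOX. A metastasis proved during treatment is therefore a post-randomisation finding. Although it is listed as an exclusion criterion, it works as a removal rule.

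**Step 2. Whether the event would be seen.** Chest CT and enhanced abdominal CT are repeated every 2 cycles (Data collection). Both arms are re-evaluated after 2 cycles, and the 4-cycle arm again after 4 (Patients and study design). The trial is equipped to find it.

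**Step 3. How the event is classified.** Take a randomised patient with new liver metastases at the 2-cycle CT and a primary tumour that has not lengthened by more than 20%.

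| Stated rule | Applies to this patient? |
|---|---|
| Progression (lengthening over 20%) | No |
| Withdrawal advice for PD, read as the same length rule | No |
| Table 1 withdrawal criteria | Not on account of the metastasis |
| Table 1 exclusion criterion 2 | Yes: removed |
| Distant recurrence, listed by pTRG | No: removed before surgery, so no pTRG |

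The patient leaves the trial and is not counted as progressed.

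**Step 4. Which arm the patient belongs to.** Under Data-analysis, 4-cycle patients who receive fewer than 3 cycles because of adverse effects or drop-out are analysed with the 2-cycle group. A 4-cycle patient whose metastasis is found after cycle 2 could fall under that rule. A progression count therefore needs to name the randomised arm explicitly.

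**Step 5. Scale, by assumption only.** Let s be the share of randomised patients who develop metastasis on CAPOX without lengthening. No value of s is in the documents. With the planned total of 554 (Sample size calculation), the number missed is s × 554:

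- s = 0.5%: 0.005 × 554 = 2.8
- s = 1%: 0.01 × 554 = 5.5
- s = 2%: 0.02 × 554 = 11.1

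**Step 6. Why the time point matters.** Time on CAPOX differs by arm. With an assumed constant risk r per cycle (also not from the documents) and 277 planned per group, the expected number by cycle c is 277 × [1 − (1 − r)^c]:

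| r per cycle | 2 cycles | 4 cycles |
|---|---|---|
| 0.25% | 1.4 | 2.8 |
| 0.5% | 2.8 | 5.5 |
| 1% | 5.5 | 10.9 |

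Even with the same risk per cycle, the 4-cycle arm shows about twice as many events up to surgery. A fair comparison between arms needs the 2-cycle assessment as well as the count up to surgery.

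**The case against.** The strongest defence is that the two rules are complementary. The progression sentence concerns the primary tumour, metastasis has its own rule in Table 1, and each event is named with a stated action. On that view only a label is in dispute. In addition, the adverse-event list is introduced as the main items and is not closed, all adverse events are to go to the registry, and the case report form and full protocol are not shown. A metastasis may well be recorded and reported under another term. Metastasis found before resection is also not a recurrence, so its absence from the distant recurrence rate is to be expected.

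Much of this stands, and it rules out three stronger readings that a reader might infer:

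- **That the narrow definition causes the removal.** It does not. Exclusion criterion 2 removes the patient and would do so under any definition of progression. The definition explains only why the patient is not counted as progressed.
- **That adverse-event reporting as a whole is too low.** The open list does not support this. Only a count made under the stated progression definition is shown to omit these patients, and the article does not promise to publish such a count separately or to compare it between arms.
- **That the primary result is affected by the definition.** Progression is not among the listed endpoints and no test of it is planned. A patient without surgery has no pTRG however progression is worded.

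What the defence does not remove is the classification itself. The article states a definition rather than leaving it to another document, and that definition leaves out a foreseeable event that the scheduled scans can detect. The remark about recurrence does not help either: it confirms that this endpoint will not pick the event up.

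**Conclusion.** The point holds as a minor one. Read literally, the stated definition of progression and exclusion criterion 2 together mean that a randomised patient with new metastases and no lengthening leaves the trial without being counted as progressed, so a progression count made under that definition omits distant progression.

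The size cannot be determined from the documents. The figures of about 3 to 11 of 554 only convert assumed shares of 0.5% to 2% and are not estimates. The conclusion assumes that the definition is applied as written. If sites use a customary PD definition that includes new lesions, or if the case report form captures metastasis as progression, the omission may not occur in practice. The pTRG3 endpoint definition and the sample size are unaffected.

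**What to change.** For adverse-event reporting:

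1. Define progression as a longitudinal increase of more than 20% or new distant metastasis on the scheduled imaging.
2. Count patients who meet exclusion criterion 2 after randomisation as progressed in their randomised arm.
3. Report the two components by randomised arm at the common 2-cycle assessment and, separately, up to surgery.

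Local or nodal worsening on the scheduled MRI or TRUS can be listed descriptively; crossing an eligibility cut-off should not by itself count as progression. The length-based withdrawal advice can stay as it is. Exclusion criterion 2 already covers metastatic patients, so no further patient would leave the trial.

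The cost is one or two sentences of wording and no new imaging. The downsides are a slightly higher reported progression rate and a reporting definition somewhat wider than the length-based PD used for withdrawal advice; the text should state that difference.

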## Methods/design

### Objective

The primary objective of this study is to prospectively evaluate that the pathological response rate after 2 cycles of CAPOX is not inferior to that of 4 cycles in patients with low-risk and intermediate-risk stage II/III rectal cancer, which may provide evidence for the feasibility of early identification of chemotherapy-insensitive population.

The secondary objectives are as follows: (1) to explore the difference in clinical remission rate between 2 and 4 cycles of CAPOX in patients with low-risk and intermediate-risk stage II/III rectal cancer; (2) to explore the effectiveness/ineffectiveness of NCT at early cycles (after 2 cycles of CAPOX) in predicting the long-term prognosis (3 years overall survival (OS)/disease-free survival (DFS)); (3) to confirm the perioperative safety of NCT alone; (4) to construct a model using 2-cycle imaging indicator to predict a 4-cycle pathological remission; and (5) to explore the feasibility of artificial intelligence (AI)-assisted imaging indicators to predict pTRG after NCT.

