### Sample size calculation

According to phase II trial [16], the proportion of patients who had poor pathological remission (pTRG 3) after 4 cycles of CAPOX was 27.9%. The proportion of pTRG3 after 2 cycles of CAPOX is expected to increase by no more than 10%. The non-inferiority test is used with *α* = 0.05, (1-β) = 0.8, and the non-inferiority margin (hazard ratio) value δ is set as 0.05. Pearson chi-square test is used to calculate the sample size required for the experiment, and 249 samples are required for each group calculated by a normal approximation algorithm [25]. Ten percent of patients are estimated to withdraw from the group or lost to follow-up; 277 patients are needed in each group. The planned enrollment time is 2.5 years, and the total number of patients is about 554 cases. Meanwhile, it is assumed that the dropout rate of patients in the 4 cycles of the CAPOX group is about 6% due to intolerance of chemotherapy. Therefore, it is estimated that 294 patients would be included in the 2 cycles of the CAPOX group and 260 patients in the 4 cycles of the CAPOX group.

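### Metastasis found on treatment and progressive disease take randomised non-responders out before pTRG3 can be graded, possibly unequally by arm

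*Protocol article*

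**What the plan says.** Under Randomization and intervention, allocation takes place once enrolment is settled, and inclusion criterion 7 bars earlier anti-tumour treatment. Every event during CAPOX therefore falls after randomisation. The Endpoints section states: "The primary endpoint is the proportion of patients with pTRG3, which is determined postoperatively by each sub-center and verified by the primary center". A patient without a resection has no grade.

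Three rules act between randomisation and surgery:

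- Progression (Monitoring and reporting): "Patients will be advised to withdraw from the trial if the tumor is determined a progressive disease (PD").
- Metastasis (Table 1, exclusion criterion 2): "Patients who do not consider metastasis in the initial diagnosis but proved to be distant metastases during the treatment".
- Intolerance (Table 1, withdrawal criterion 2): "Patients having severe adverse reactions to chemotherapy and being unable to complete 2 cycles of chemotherapy".

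Data-analysis adds a fourth: a 4-cycle patient who receives fewer than 3 cycles because of adverse effects or drop-out is analysed in the 2-cycle group.

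The Sample size calculation provides for departures only as a loss: "Ten percent of patients are estimated to withdraw from the group or lost to follow-up". Patients and study design gives the 2-cycle arm one re-evaluation and the 4-cycle arm two. The Objective says the comparison is one "which may provide evidence for the feasibility of early identification of chemotherapy-insensitive population".

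**The concern.** Progression or new metastasis during chemotherapy is the plainest sign of chemotherapy insensitivity. If such patients leave before surgery and nothing replaces the missing grade, pTRG3 is estimated in a group already selected on response. Two consequences follow.

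First, non-response is understated in each arm, although a stated aim is to obtain the response rate after 2 cycles. Second, if the arms lose different shares, the between-arm difference is distorted. The 4-cycle arm has a longer preoperative window and one more scan, so there is more opportunity to find progression there.

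The rules also conflict. A 4-cycle patient who cannot complete 2 cycles is withdrawn under Table 1 but analysed in the 2-cycle group under Data-analysis. A 4-cycle patient who progresses at the first re-evaluation is advised to leave under Monitoring and reporting, yet may count as a drop-out with fewer than 3 cycles and so be moved. A 2-cycle patient with the same early event has no such route.

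**Working it through.** **Inputs from the Sample size calculation.** Poor remission (pTRG3) "after 4 cycles of CAPOX was 27.9"%. Allowed increase: "The proportion of pTRG3 after 2 cycles of CAPOX is expected to increase by no more than 10"%. Power is 0.80, α 0.05, 249 per group, and 277 after 10% loss.

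**The plan's own figure.** With 27.9% in both arms, a 10-point margin and one-sided 0.05:

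n = 2 × 0.279 × 0.721 × (1.645 + 0.842)² / 0.10² = 248.7, so 249. Then 249 / 0.90 = 276.7, so 277.

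The stated figures reproduce. (They need a 10-point margin, not the δ of 0.05 labelled a hazard ratio; that is a separate matter.)

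**Effect of removal.** The documents give no progression or metastasis rates, so the removal rates are assumptions. A share a of an arm is removed, all of them failures, and 27.9% is taken as total non-response. Then:

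- observed rate = (p − a) / (1 − a)
- evaluable n = 249 × (1 − a)
- SE = √[p₂(1 − p₂)/n₂ + p₄(1 − p₄)/n₄]
- P(non-inferiority) = Φ[(0.10 − difference)/SE − 1.645]

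True rate 27.9% in both arms:

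| Removed, 2-cycle v 4-cycle | Observed rates | Difference | SE | Power |
|---|---|---|---|---|
| 0% v 0% | 27.9% v 27.9% | 0 | 0.0402 | 80% |
| 2% v 2% | 26.4% v 26.4% | 0 | 0.0399 | about 81% |
| 2% v 4% | 26.4% v 24.9% | +1.5 points | 0.0397 | about 69% |
| 3% v 6% | 25.7% v 23.3% | +2.4 points | 0.0394 | about 61% |

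Example, 2% v 4%: (0.279 − 0.02)/0.98 = 0.264; (0.279 − 0.04)/0.96 = 0.249; Φ[(0.10 − 0.0153)/0.0397 − 1.645] = Φ(0.49) = 0.69. If 249 evaluable per arm is kept, because 277 already allows for losses, the last two powers are 70% and 63%.

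True rates 37.9% v 27.9%, so that 2 cycles is exactly 10 points worse:

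| Removed, 2-cycle v 4-cycle | Observed difference | False non-inferiority |
|---|---|---|
| 0% v 0% | 10.0 points | 5% |
| 2% v 4% | 11.7 points | about 2% |
| 4% v 2% | 8.9 points | about 8% |

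**Cost of counting these patients.** If 27.9% is instead the pTRG3 rate among resected patients and 4% progress, the combined control rate is 0.04 + 0.96 × 0.279 = 0.308. The same formula with 0.308 × 0.692 gives 263.5, so 264 per arm. With 249, power is about 78%.

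**The case against.** **Removal from the analysis is inferred.** No section says withdrawn patients leave the numerator and denominator, withdrawal on progression is only advised, and analysis sets are commonly left to the SAP or full protocol. This stands as a limit on certainty. But the article itself fixes the exclusion, the withdrawals and the reassignment, and a later SAP cannot recover outcomes from patients who have left.

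**The bias is probably conservative.** This largely stands. A reader might infer that the rules make a false claim of non-inferiority more likely. More removals in the 4-cycle arm do the opposite; inflation needs heavier removal in the 2-cycle arm, for which the design gives no reason.

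**Early intolerance is not insensitivity.** This stands. It would be easy to group all three removals as loss of insensitive patients, but failing 2 cycles through severe reactions is toxicity, and that window is common to both arms. The calculations above do not describe this group; its problem is the conflicting handling.

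**Survival results.** A reader might infer that these patients are also lost to DFS and OS. The documents do not establish that: survival endpoints are defined by pTRG group, in which an unresected patient has no place anyway, and long-term follow-up is promised with no stated end at progression.

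**A combined endpoint changes the question.** This stands in part. Progression in cycles 3 and 4 could count only against the 4-cycle arm. If the resected pTRG3 gap is truly 10 points and 2% v 4% progress, the combined gap is (0.02 + 0.98 × 0.379) − (0.04 + 0.96 × 0.279) = 8.4 points, and non-inferiority would be declared about 10% of the time with 249 per arm. The resected-only result must therefore sit beside it.

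**Conclusion.** The concern holds for progression and on-treatment metastasis. Rules written into the protocol article remove clear non-responders after randomisation and before the endpoint exists, with no provision to count them and with unequal opportunity by arm. The rules on early departure also contradict one another.

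The size is not known. Under the assumed rates, the spurious difference is +1.5 to +2.4 points against a 10-point margin, with power about 69% to 61% instead of 80%. With equal removal the comparison is nearly unaffected, but each arm's non-response is still understated (26.4% instead of 27.9% at 2%). These figures assume that every removed patient is a failure and that 27.9% is total non-response. The stated sample size contains no arithmetic error on this point. The protocol should be amended; confidence is moderate, because the removal rates, and whether advised withdrawals leave the analysis, are not documented.

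**What to change.** 1. Do not apply exclusion criterion 2 after randomisation.
2. Separate stopping study treatment, which stays with the existing clinical rules, from leaving the trial. Reserve the latter for withdrawn consent and true loss, and let the 10% allowance refer to those.
3. Keep all randomised patients in follow-up and analyse them in their randomised arm. Reconcile Table 1, Data-analysis and Monitoring and reporting so that one event is handled one way in both arms.
4. In the primary analysis, count progression, new metastases or no resection for disease reasons as non-response together with pTRG3. Report pTRG3 among resected patients alongside, and discuss any disagreement between the two.
5. Describe toxicity withdrawals separately by arm, not as chemotherapy insensitivity.
6. Restate the power for the combined rate.

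The cost is mainly wording, since follow-up visits already exist, but it is not nil. The combined endpoint is a different quantity from pTRG3 alone, its rate is somewhat higher, and precision at the same margin is slightly lower: for a control rate of about 31%, roughly 264 per arm instead of 249, or about 78% power if 249 is kept.

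### For grade 3 reactions outside the digestive tract, adjacent toxicity rules give incompatible actions: one ends treatment, the next manages the reaction as grade 2

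*Protocol article*

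**What the plan says.** The rules stand in the Protocol article under Monitoring and reporting. The letters are mine.

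- **A, general rule.** "If a 1/2° adverse reaction occurs, no special treatment is required". No exception is written.
- **B, listed reactions.** "Capecitabine/oxaliplatin should be discontinued and corresponding symptomatic treatment should be given when 4° leukopenia, 3° adverse reactions of the digestive tract", and the list continues: "2° anemia and thrombocytopenia, and 2° liver and kidney function impairment occur". If the reaction falls to grade 0 or 1 within five days, "the original dose of capecitabine/oxaliplatin can be restored"; otherwise the dose is cut to 75%.
- **C, end of the same item.** Treatment is discontinued if the listed reactions last more than three days despite supportive care and a dose cut, or if "other adverse reactions above 2° occur". No restart is described.
- **D, other grade 3 reactions.** "When other 3° adverse reactions occur, the treatment principle is the same as the corresponding 2° adverse reactions".
- **E, grade 4.** "Chemotherapy should be stopped in case of any 4° adverse reactions other than leukopenia occurring".

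Two other places make the number of cycles matter. Under Data-analysis, a patient in the 4-cycle arm who gets fewer than three cycles because of adverse effects or dropout is analyzed with the 2-cycle group. In Table 1, being unable to complete two cycles because of severe reactions is a withdrawal criterion.

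**The concern.** C and D stand next to each other and both speak of other reactions. Grade 3 is above grade 2, so both apply to the same event, and they do not give the same answer. Fourteen hospitals are to apply these rules, and each sub-center monitors the safety of its own patients. Two centers could each follow a sentence of the protocol faithfully and treat the same reaction differently.

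This is first a safety matter. It also reaches the analysis, because exposure decides who is counted in which group and who is withdrawn, and because adverse effects of chemotherapy are a secondary endpoint.

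**Working it through.** No arithmetic applies, and the plan gives no figure to reproduce. The check is to apply each rule to each type and grade of reaction and compare the actions.

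| Reaction | Under C | Under D | Under A, B or E directly | Result |
|---|---|---|---|---|
| Grade 3 anemia, thrombocytopenia, liver or kidney impairment | Stop | As grade 2, so B: hold, restart possible | Not listed at grade 3 | Stop versus hold |
| Grade 3, type not listed anywhere | Stop | As grade 2, so A: no action | None | Stop versus no action |
| Grade 3 leukopenia | Stop | As grade 2, so A: no action | Listed in B only at grade 4 | Stop versus no action |
| Grade 4 leukopenia | Listed, so not an other reaction | Not grade 3 | B: hold, restart possible; exempt from E | Hold |
| Grade 3 digestive tract | Listed, so not an other reaction | Listed, so not an other reaction | B: hold, restart possible | Hold |
| Grade 4, except leukopenia | Stop | Not grade 3 | E: stop | Stop |
| Grade 2 anemia, thrombocytopenia, liver or kidney impairment | Not above grade 2 | Not grade 3 | A: no action; B: hold | Hold, if B is an exception to A |

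**Conflict.** The first three rows have two incompatible actions each. I assume that the word *other* has the same reach in C and D; nothing in the text separates them.

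**Order of severity.** Set rows three and four side by side. Under C, grade 3 leukopenia ends treatment with no described restart. Under B, grade 4 leukopenia is an interruption after which the full dose may return. On the literal text the lower grade can receive the stricter action.

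**Narrower reading of C.** Suppose that C applies only once the dose has been reduced. A patient on the 75% dose then develops a new grade 3 reaction of an unlisted type. C ends treatment; D sends the reaction to the grade 2 principle. The overlap is smaller, but the conflict is still there.

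**Reach into the analysis.** Take a patient in the 4-cycle arm who has finished the drugs of cycle 2 and has a grade 3 laboratory reaction at the weekly blood test. Under C the patient stops with two cycles; 2 is less than 3, so the patient is analyzed with the 2-cycle group. Under D the patient may go on and, with three or more cycles, is analyzed in the 4-cycle group. In either arm, a stop during the first cycle can meet the Table 1 withdrawal criterion, whereas management under D need not. A temporary hold does not by itself reduce the number of cycles, and a stop after the third cycle does not change the group.

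**The case against.** The strongest reply is that the text is a flattened four-item list: grade 1/2, listed reactions, other grade 3, and grade 4. On that view C closes the second item, and its wording, "dosage reduction or other adverse reactions above 2° occur", belongs to the end of the hold-and-reduce sequence, while D governs a first grade 3 reaction. This is a fair reading and it narrows the problem. It does not remove it, because nothing limits the second half of C to patients already reduced and, even if it did, C and D still disagree for those patients. That the article condenses a longer protocol excuses omissions, but not two stated rules that clash.

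Other parts of the reply stand in full, and they rule out stronger readings that a reader might infer:

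- **That a grade 2 patient could be continued, held or stopped.** No sentence gives an initial stop at grade 2. The named grade 2 reactions in B read naturally as a specific exception to A; otherwise naming them would serve no purpose. At most the split is continue versus hold.
- **That grade 3 anemia, thrombocytopenia, liver or kidney impairment could also simply continue.** That needs A to override B at grade 2, which is the strained reading.
- **That the two uses of *discontinued* leave hold and stop indistinguishable.** Context largely separates them: the first is followed at once by the conditions for restarting, the second comes after a failed reduction.
- **That the 6% intolerance assumption, which moves the expected groups from 277 each to 294 and 260, depends on these rules.** Sample size calculation states it as a planning assumption, and nothing there derives it from the toxicity rules.

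**Conclusion.** The point holds for grade 3 reactions outside the digestive tract. The documents prescribe discontinuation in one sentence and, in the next, a hold with possible restart (anemia, thrombocytopenia, liver and kidney impairment) or no action (unlisted types, and leukopenia on a literal reading). The leukopenia inversion follows from the same clash.

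Two lesser wording points go with it: A does not say that the listed grade 2 reactions are exceptions, and one word serves for both a temporary hold and a later stop. Grade 3 digestive tract reactions, and the choice between hold and stop at grade 4, are not in conflict.

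The size is unknown, because the documents give no frequency for any of these reactions. The effect on group membership runs only through stops before a third cycle in the 4-cycle arm, and the effect on withdrawal only through stops before two cycles are completed. The conclusion rests on the published text and on reading *other* alike in C and D.

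**What to change.** The sponsor's clinical team should reconcile the sentences under Monitoring and reporting so that each reaction type and grade leads to one action. In particular:

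- Resolve C against D for grade 3, and check the result against the handling of leukopenia at grades 3 and 4.
- State whether the listed grade 2 reactions are exceptions to the general grade 1/2 sentence.
- Use one word for a temporary hold and another for a permanent stop.
- Send the reconciled text to all centers.

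The content of each rule is for the clinical team; this review takes no side.

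The cost is a short amendment, submitted for approval as Protocol amendments requires, and a memo to centers. Its reach is limited by time: the article appeared in June 2023 and recruitment, begun in June 2021, was expected to end in December 2023. The amendment therefore helps only patients still to be treated. For those already treated, recording the reason for each stop would at least show whether practice differed between centers.
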